Bekedam et al. used electromagnetically tracked ultrasound imaging to scan eight tongue cancer specimens immediately after excision [21]. The specimen and the tumor were segmented manually by a radiologist, and the margins were computed in 3D by calculating the closest Euclidean distances between the segmented specimen and the tumor boundary. The borders were more difficult to distinguish in some of the specimens due to small echogenicity differences between the tumor and healthy tissue. Even though the use of electromagnetic sensors is one of the most cost-effective methods for localization in freehand 3D ultrasound systems, their main drawback is their metal sensitivity [20]. Table 2 summarizes some of the publications focusing on surgical margin assessment.

In the current protocol, we introduce a novel approach to the assessment of resection margins in tongue SCC. We propose the application of 3D ex vivo ultrasound using a mechanical arm and a custom-made setup (3Sonics). This technique represents a significant advancement in the field, as it offers a portable, cost-effective, and efficient alternative to existing 3D ultrasound imaging methods. Unlike other imaging techniques, our proposed 3D ultrasound imaging technique does not rely on any type of sensor for probe position tracking, simplifying its operation and potentially increasing its accessibility and usability in various clinical settings. 

Furthermore, our method allows for a comprehensive comparison of the 3D ultrasound outcomes with results from MRI and clinical examination of the surgical specimen by a surgeon. This multi-modal approach enhances the robustness of our study and provides a more comprehensive understanding of the resection margins. The diagnostic accuracy of our method will be evaluated by computing the correlation of these three approaches to the final histopathology report, the gold standard in cancer.

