## 4. Clinical Outcome Definition

We will compare the surgical margin assessment in tongue cancer specimens by comparing three index tests (clinical examination, 3D ultrasound, and MRI) with the post-surgical histopathology assessments as the reference standard. 

The primary outcome will be reported as:The perioperative measurement of resection margins (mm) at five directions (Figure 1) with clinical exam and imaging compared to the post-surgical histopathology results (reference standard).The image-by-image comparison of the depth of invasion measurement (mm) from 3D ultrasound/MR imaging and histopathology slides.The depth of invasion (mm) comparison between in vivo and ex vivo ultrasound.The number of margins correctly classified as free (>5 mm), close (1–5 mm), or positive (<1 mm) margins by 3D ultrasound and MRI using histopathology findings as the reference.

The secondary outcome will be: The number of cases requiring adjuvant treatments (surgery or chemo/radiotherapy) due to T-site residuals.A change in tumor volume and resection margin measurements with 3D ultrasound imaging before and after formalin fixation.The time usage (minutes) and cost estimation for perioperative 3D ultrasound and MRI.

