## 5. Statistics

There will be three index tests used for clinical examination, 3D ultrasound imaging, and MRI of the ex vivo specimen. The reference standard will be the final histopathology result. Each case will undergo five margin measurements (anterior towards the apex of the tongue, posterior towards the base of the tongue, medial, lateral, and profound/deep margins) by three index tests and one standard reference. Tumor and specimen volume will be calculated for each case. The deep margin will be measured at equally distanced planes of imaging in every case, and the results will be correlated to the corresponding deep margin measurements from the reference standard.

The participants will be excluded from the final analysis in case of any technical issues such as non-feasibility to perform parallel slicing of the surgical specimen or patients with MRI contradictions (pacemaker, metal implants not compatible with MRI, etc.). The number of excluded participants will be reported as non-conclusive cases and will be excluded from the study.

Margin measurements (quantitative data in mm) and tumor and specimen volume measurements (quantitative data in ml) will be presented as an averaged value over two measurement repetitions, as described in Section 3.2. The measurement differences between the index tests and the reference standard will be compared by a paired *t*-test. The degree of correlation will be expressed using Pearson’s correlation coefficient, in which the index tests and the reference standard will be considered to be significantly correlated when *p* < 0.05. To evaluate the agreement between the index tests and the reference standard, we will also analyze the data using Bland–Altman plots, which show the mean difference between the two techniques with a 95% confidence interval. This allows for easy interpretation of whether the differences between the index tests and the reference standard are clinically relevant. Correlation between the plane-by-plane deep margin measurements obtained by the reference standard and the index tests will be evaluated by *t*-test, and the threshold for significance correlation will be *p* < 0.05. The correlation between the depth of invasion measurements (mm) from in vivo ultrasound and the ex vivo ultrasound will also be reported.

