The intra- and interobserver variability will be quantified by calculating the intraclass correlation coefficient (ICC). The ICC measures the reliability of the measurements between the two observers and is the measure of the degree of agreement among the observers in their assessment of margin status.

We will also classify the data into three categories of positive (<1 mm), close (between 1–5 mm), and free (>5 mm) margins. For each included case, we will compare the accuracy of each index test by computing the proportion of correctly classified margins with respect to the reference standard class. We will use the McNemar test to determine if the proportions of categories in the index tests differ significantly from those of the reference standard (paired categorical data). The results will be considered statistically significant when *p* < 0.05, with a 95% confidence interval. 

The mean time spent on delineation by the operators will be recorded and reported in minutes. Data will be analyzed with commercially available software (RStudio Team-2023). RStudio: Integrated Development for R. RStudio, Inc., Boston, MA, USA.

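### The Bland–Altman interval, the plane-by-plane t-test and the use of correlation as accuracy do not, as worded, measure how closely a single margin is measured in mm

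*Protocol article*

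**What the plan says.** The first primary outcome in Section 4 is a measurement comparison: "The perioperative measurement of resection margins (mm) at five directions (Figure 1) with clinical exam and imaging compared to the post-surgical histopathology results". Section 5 (Statistics) then gives the analyses that bear on it:

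- Paired *t*-test: "The measurement differences between the index tests and the reference standard will be compared by a paired" *t*-test.
- Pearson's coefficient: "the index tests and the reference standard will be considered to be significantly correlated when" *p* < 0.05.
- Bland–Altman, the one method that the section names for agreement: "plots, which show the mean difference between the two techniques with a 95% confidence interval". The next sentence adds: "This allows for easy interpretation of whether the differences between the index tests and the reference standard are clinically relevant".
- Plane-by-plane deep margin: "Correlation between the plane-by-plane deep margin measurements obtained by the reference standard and the index tests will be evaluated by" a *t*-test, with *p* < 0.05 as the threshold.
- Classification into positive, close or free, by "computing the proportion of correctly classified margins with respect to the reference standard class". Section 4 lists this as a primary outcome for 3D ultrasound and MRI.

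The ICC in Section 5 is for observer variability, not for index test against histopathology. The Introduction says that diagnostic accuracy "will be evaluated by computing the correlation of these three approaches to the final histopathology report". The end of Section 3.2.2 likewise correlates the ultrasound measurements with histopathology in order to judge their accuracy.

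**The concern.** For a margin in mm, a reader needs to know how far one reading on one specimen may lie from the histopathology value. Three of the rules, followed as written, answer something else.

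1. A 95% confidence interval for the mean difference shows how well the average bias is known. It shrinks with the number of patients even if single readings scatter as widely as before, so clinical relevance for an individual margin cannot be read from it.
2. A *t*-test that compares two measurement series tests whether their means differ. It does not assess their correlation or their agreement.
3. Correlation is not accuracy. Pearson *p* < 0.05 rejects only a true correlation of zero, and a constant offset between the methods leaves *r* unchanged.

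At stake is the reported result for a listed primary outcome: it could be a narrow interval or a significant correlation that says little about the error of a single measurement.

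**Working it through.** **Inputs.** Section 6 gives 27 evaluable cases (30 with 10% drop-out). Each case gives one margin per direction, so a single direction has 27 pairs. The SD of the differences (index test minus histopathology) is not given; a range of 1 to 4 mm is assumed.

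The document gives no figure for agreement to reproduce. The 27 itself can be reproduced with the formula for two independent proportions, unpooled variance, two-sided 0.05 and 90% power, as a per-group size: (1.960 + 1.282)² × (0.55 × 0.45 + 0.16 × 0.84) / 0.39² = 26.4, rounded up to 27. It is used here only as the number of pairs; it was not chosen for precision of agreement.

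**Step 1: interval for the mean difference.** Half-width = t(0.975, n−1) × SD / √n. At n = 27: 2.056 × SD / 5.196 = 0.396 SD.

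**Step 2: limits of agreement.** Half-width = 1.96 × SD.

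**Step 3: ratio.** 1.96 / 0.396 = 4.95, about 5, whatever the SD. At n = 30 it is 1.96 / 0.373 = 5.2.

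| Assumed SD (mm) | 95% CI of mean, n = 27 (mm) | 95% limits of agreement (mm) |
|---|---|---|
| 1 | ±0.40 | ±1.96 |
| 2 | ±0.79 | ±3.92 |
| 3 | ±1.19 | ±5.88 |
| 4 | ±1.58 | ±7.84 |

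**Step 4: precision of each limit.** Half-width = t × SD × √(1/n + 1.96² / (2(n−1))). At n = 27: 2.056 × √(0.0370 + 0.0739) × SD = 0.68 SD, for example ±1.37 mm at SD 2 mm. The limits should therefore be shown with their own intervals.

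**Step 5: the Pearson threshold.** Critical |r| = t / √(n − 2 + t²), with t(0.975, 25) = 2.060. At n = 27: 2.060 / √(25 + 4.24) = 0.38, or r² of about 0.15. Significance can thus be reached with about 15% shared variance.

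**Step 6: illustration by simulation.** 20,000 data sets of 27 pairs, with an assumed true-margin SD of 3 mm:

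| Error SD, bias (mm) | t-test not significant | Pearson significant | Single error > 2 mm |
|---|---|---|---|
| 1, 0 | 95% | 100% | 4.5% |
| 2, 0 | 95% | > 99.9% | 32% |
| 3, 0 | 95% | 99% | 51% |
| 0.3, 0.5 | 0% | 100% | 0% |

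The first three rows look almost the same on the *t*-test and the Pearson *p*-value, although the proportion of single errors above 2 mm rises from 4.5% to 51%. In the last row a very precise method with a small offset always gives a significant *t*-test.

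**Step 7: the plane-by-plane rule.** If the *t*-test compares the two series, it tests the mean difference and not the correlation. If it means the *t*-test of r = 0, it is the Pearson test of Step 5 again. Neither reading gives agreement.

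**The case against.** The strongest reply has four parts.

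*Bland–Altman is the right method, and the wording may simply be loose.* Such a plot shows every difference and by convention carries limits of agreement, so the 95% interval may be shorthand for them. This is fair, and if so the repair is one sentence. But the text attaches the interval to the mean difference and then reads clinical relevance from it. Loose wording also does not explain the *t*-test for correlation or the Introduction's account of accuracy.

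*The plan does not judge agreement by the t-test or the Pearson p-value.* This stands. A reader might infer that it does, but Section 5 gives agreement to Bland–Altman alone, calls a Pearson result only significantly correlated, and nowhere treats a non-significant *t*-test as agreement.

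*Single margins are covered by the classification analysis.* This stands in part. That analysis uses the 1 and 5 mm cut-points, and large errors would tend to appear as wrong classes. But it works by category: 4.9 mm read as 1.1 mm counts as correct although 3.8 mm off, and 5.1 mm read as 4.9 mm counts as wrong although 0.2 mm off. It does not replace the comparison in mm, which is a separate primary outcome.

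*Some detail belongs in the analysis plan, and some is preference.* This also stands. A tolerance in mm may be set in an analysis plan that is not shown. An absolute-agreement ICC is one option among several. Pearson's *r* as a descriptive supplement does no harm.

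**Conclusion.** The point holds for three statements: the interval in the Bland–Altman sentence and the clinical reading given to it, the plane-by-plane *t*-test, and the Introduction's equation of accuracy with correlation. Followed literally, they give the wrong quantity for a listed primary outcome. The interval for the mean is about one fifth as wide as the limits of agreement at 27 cases. That ratio does not depend on the SD; the values in mm do, and rest on an assumed 1 to 4 mm. The simulation also rests on an assumed true-margin SD.

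Two stronger conclusions are tempting but unsupported. The first is that the study could declare a method accurate despite errors wider than the close class. The document states no rule for such a declaration and plans the classification analysis. At an assumed SD of 2 mm the limits of ±3.92 mm are still within the 4 mm class width, and only 4.5% of simulated errors exceed 4 mm. The second is a much larger ratio, or a lower critical *r*, from pooling all margins or planes as independent; Section 5 does not say that they will be pooled in this way.

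This should be corrected before analysis. It does not call the data collection into question.

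**What to change.** - Section 5, Bland–Altman: replace the confidence interval of the mean difference with the bias and the 95% limits of agreement for each index test, each with a 95% confidence interval that allows for several margins per patient. Tie the statement on clinical relevance to the limits.
- Section 5, plane-by-plane deep margin: replace the *t*-test with the same limits-of-agreement analysis, allowing for several planes per patient.
- Section 5, Pearson: keep *r* as a descriptive figure and drop *p* < 0.05 as evidence of accuracy.
- Introduction: change correlation to agreement where diagnostic accuracy is defined, and align the similar sentence at the end of Section 3.2.2.

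The cost is analysis wording and slightly more analysis work; no further patients or measurements are needed. The drawback is a less favourable-looking interval, about 5 times wider than the one now described, with each limit uncertain by about ±0.68 SD at 27 cases.

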## 1. Introduction

Oral squamous cell carcinoma (SCC) is the eighth most common cancer worldwide, with less than 60% of the patients surviving more than 5 years [1]. In a study conducted at our center (Department of Otorhinolaryngology, Head and Neck Surgery, and Audiology, Rigshospitalet, University of Copenhagen, Copenhagen, Denmark), among 8299 oral cancer patients, it was found that the 5-year overall survival rate was 43% for women and 36% for men [2]. SCC of the tongue is the most common type of oral cavity cancer, and the primary treatment for patients with early stages of tongue SCC is surgery [3,4]. The main goal of surgical oncology is to entirely remove the tumor, along with a margin of healthy tissue surrounding it, to ensure proper cancer removal. At the same time, preserving as much healthy tissue as possible during tongue cancer surgery ensures the quality of life for the patient, maintaining vital functions such as swallowing and speaking after surgical treatment. Survival and the need for postoperative treatment are highly dependent on the accuracy of the surgical resection margins for the cancer. Inadequate surgical margins (margin ≤ 5 mm) may lead to a second resection [5]. The presence of positive (<1 mm) or close (1–5 mm) margins following cancer surgery leads to an increased risk of local cancer recurrence, reduces the chance of survival, and necessitates adjuvant treatments, such as radiotherapy or chemoradiation. In a study at our center investigating 1399 patients with oral squamous cell carcinoma (OSCC), 44% of the cases received adjuvant radiotherapy after surgery [6]. A recent retrospective analysis of 91 tongue SCC resections reported a total of 74% of the cases with close margins (1–5 mm) and 10% with positive margins (<1 mm) [7]. Given the significant impact of surgical precision on patient outcomes in oral squamous cell carcinoma (SCC), there is a pressing need for advanced intraoperative techniques to ensure complete tumor resection. The potential for positive surgical margins, which can lead to the necessity for additional treatments or even further surgery, underscores the critical need for more accurate and efficient intraoperative techniques. Therefore, the development and implementation of innovative approaches that can improve the rate of complete tumor resection are not only desirable but essential for enhancing surgical care and ultimately improving patient survival rates and quality of life [8].

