#### 3.2.4. Tissue Preparation and Histopathology

After conducting the MRI scan in the radiology department, the surgical specimen will be returned to the pathology department for formalin fixation. 

In the pathology department, the samples will be treated using standard procedures to create formalin-fixed, paraffin-embedded (FFPE) blocks of tissue. The samples are first formalin-fixed with 10% formaldehyde for 24 h. Before starting the slicing procedure of the specimen by the pathologist, the formalin-fixated specimen will again undergo 3D ultrasound. Then a pathologist will perform parallel slicing, with almost equal intervals (~2 mm). The slices are then transferred to cassettes for further processing and embedded in paraffin to form FFPE blocks, which are cut at 4 μm and mounted on glass slides. Afterwards, the slides will be stained with hematoxylin and eosin (H&E) to visualize the tissue under the microscope. Two pathologists will assess the surgical margin status and will delineate the tumor on the slides. The tumor volume in milliliters (mL) will be estimated by the multiplication of the tumor area per slice and the cutting intervals. The pathologist will also measure the smallest margin at the posterior, anterior, lateral, medial, and profound directions (as described in Figure 1). The average measurement obtained by the two pathologists will be considered as the gold standard.

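### One Bland–Altman mean difference shows the error at the 5 mm and 1 mm margin limits only if bias and scatter do not change with margin size, and the plan includes no check of this

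*Protocol article*

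**What the plan says.** The first primary outcome in Section 4 of the protocol article is the margin in mm in five directions, by clinical examination and imaging, against histopathology. For agreement, Section 5 plans Bland–Altman plots, "which show the mean difference between the two techniques with a 95% confidence interval", and says of them: "This allows for easy interpretation of whether the differences between the index tests and the reference standard are clinically relevant". It states no acceptable difference in mm and no analysis of whether the difference varies with margin size.

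The clinical limits are fixed elsewhere. The Introduction and Sections 4 and 5 define positive as below 1 mm, close as 1–5 mm and free as above 5 mm. Classification is a separate primary outcome in Section 4: "The number of margins correctly classified as free (>5 mm), close (1–5 mm), or positive (<1 mm) margins by 3D ultrasound and MRI". Section 5 analyses it by "computing the proportion of correctly classified margins with respect to the reference standard class", plus McNemar tests.

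On tissue state, Sections 3.2.1 to 3.2.3 place the surgeon's examination, the first 3D ultrasound and the MRI before fixation. For the reference, Section 3.2.4 says: "The samples are first formalin-fixed with 10% formaldehyde for 24 h". Paraffin embedding follows. A secondary outcome in Section 4 is "A change in tumor volume and resection margin measurements with 3D ultrasound imaging before and after formalin fixation".

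**The concern.** A mean difference averages over all margins in the sample. It equals the bias at 5 mm only if bias is constant over margin size, or if the sample happens to be centred so that the two coincide. Likewise, one measure of spread applies at 5 mm only if scatter is constant.

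If tissue changes by a roughly constant percentage between the fresh scan and the slide, the difference in mm grows with the margin. The pooled figure then describes the average margin in the sample and not the margins at which a class changes. A test could be judged clinically unacceptable, or acceptable, on error that does not apply near 5 mm. Section 5 invites this reading because it ties clinical relevance directly to the overall figure.

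**Working it through.** **Plan's own figure.** The protocol gives no expected bias, standard deviation or limits of agreement, so there is nothing to reproduce. The figures below illustrate the mechanism and rest on assumptions.

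**Inputs**
- Limits of 1 mm and 5 mm: protocol, Sections 4 and 5.
- Target of 30 cases with five directions each: Sections 5 and 6, so at most 30 × 5 = 150 margins.
- Assumed: histology margin H = F(1 − s), where F is the fresh margin and s = 0.15.
- Assumed: F lognormal with log-SD 0.6 and median 4, 5, 6 or 8 mm.
- Assumed: index-test error SD = 0.5 mm + 0.15F.

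**Step 1: bias at a given histology value.** Bias(H) = H·s/(1 − s).
- At 5 mm: 5 × 0.15/0.85 = 0.88 mm.
- At 1 mm: 1 × 0.15/0.85 = 0.18 mm.

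**Step 2: pooled bias.** Pooled bias = s × mean(F), with mean(F) = median × exp(0.6²/2) = median × 1.197.

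| Median F (mm) | Pooled bias (mm) | Pooled ÷ bias at 5 mm |
|---|---|---|
| 4 | 0.72 | 0.81 |
| 5 | 0.90 | 1.02 |
| 6 | 1.08 | 1.22 |
| 8 | 1.44 | 1.63 |

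The ratio equals mean(H)/5 whatever s is. The pooled figure is therefore too small, about right or too large at 5 mm according to the mix of margins. At 1 mm the ratio is mean(H)/1, so the pooled bias is about 4 to 8 times the bias there (0.72/0.18 to 1.44/0.18).

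**Step 3: spread, median 6 mm.**
- Var(F) = 36 × exp(0.72) − 7.18² = 73.96 − 51.60 = 22.36.
- Shrinkage contributes 0.15² × 22.36 = 0.50.
- Measurement error contributes 0.25 + 0.15 × 7.18 + 0.0225 × 73.96 = 2.99.
- Pooled half-width: 1.96 × √3.49 = 3.66 mm.
- At H = 5 mm, F = 5/0.85 = 5.88 and SD = 0.5 + 0.88 = 1.38, so the half-width is 2.71 mm.

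With no shrinkage, the pooled half-width is 1.96 × √2.99 = 3.39 mm against 1.96 × 1.25 = 2.45 mm at 5 mm. With 15% shrinkage but a constant 1 mm error SD, it is 1.96 × √1.50 = 2.40 mm against 1.96 mm. Most of the gap in spread therefore comes from the assumed growth of measurement error with distance.

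**Step 4: choice of axis.** Simulating the 6 mm case and regressing the difference on the mean of the two methods gives a bias of about 0.70 mm at 5 mm and about −0.2 mm at 1 mm. By histology value the figures are 0.88 and 0.18 mm. At small margins the two axes disagree in sign.

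**Step 5: can it be estimated?** In the same case, treating 150 margins as independent, the standard error of the regression bias at 5 mm is about 0.1 mm. About 2% of histology margins lie below 1.5 mm, which is about 3 of 150. Clustering within specimens would usually widen the standard error.

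**The case against.** Several objections carry weight.

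- **Proportional change is not in the protocol.** A reader might infer from the fixation outcome that the plan expects a change that scales with size. Section 4 lists only a change to be measured and gives no direction, amount or proportionality. Proportionality is an assumption of this check. Error that grows with distance is also an assumption.
- **Dominance by wide margins is not shown.** A reader might infer that wide margins drive the pooled result. That depends on the unknown distribution: the gap in bias at 5 mm vanishes at a median of 5 mm and reverses at 4 mm. The Introduction cites a series with 74% close and 10% positive margins, so 84% of cases were at or below 5 mm. That is a figure per case, so it does not settle the mix across five directions.
- **The limits have their own outcome.** Correct classification is a primary outcome. This reduces what rests on the mean difference, but proportion correct and McNemar give no error in mm at the limits.
- **A plot displays a trend.** This is true, and the plan does not say that the five directions are pooled into one figure. But the summary that it names for judging relevance would not carry the trend.
- **Modelling detail belongs in an analysis plan.** Regression-based limits could reasonably be left there. The point here is the article's explicit claim that clinical relevance follows easily from the stated summary.

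A reader might also infer that the pooled bias will be used to recalibrate margins. No such step is planned.

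**Conclusion.** The concern holds in a limited form. Section 5 claims more for the mean difference than it can show unless error is constant over margin size, and the different tissue states of index test and reference make constancy doubtful enough to check. Under the assumptions above, the pooled bias differs from the bias at 5 mm by −0.16 mm (0.72 − 0.88) to +0.56 mm (1.44 − 0.88) for medians of 4 to 8 mm. At 1 mm it is too large throughout that range. The pooled spread also overstates spread at 5 mm in the 6 mm case, by an amount that depends mainly on the assumed error model. The documents do not fix the direction or the size of the misstatement, so this is an improvement to make and not a demonstrated bias in the trial's result.

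**What to change.** In Section 5, keep the overall Bland–Altman plot and mean difference as description. Then add:

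- For each index test, check whether the difference and its spread depend on margin size, with specimen as cluster.
- If they do, report regression-based (or log-ratio) bias and 95% limits of agreement at 5 mm, and judge clinical relevance there.
- Report 1 mm as exploratory, with its confidence interval and the number of margins near it.
- Show results against the histology value as well as against the mean of the two methods, because the two axes can differ in sign at small margins.

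The cost is a few sentences in the plan and a short piece of extra analysis in R, with no new data. The downside is that estimates at 1 mm will be imprecise.

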Following the surgery, two experienced head and neck surgeons will manually segment the tumor region on the 3D ultrasound images. This process will involve identifying and delineating the tumor boundaries based on the echogenicity differences between the tumor and the surrounding healthy tissue. Segmentation will be conducted using the ITK-SNAP segmentation software (www.itksnap.org (accessed 5 on July 2023)) [48], a widely used and validated tool for medical image segmentation. The surgeons will measure the smallest margin (anterior, posterior, lateral, medial, and deep margin). The segmentation process will be performed on approximately 10–15 equally distanced planes throughout the tumor volume. These planes will be selected to provide a comprehensive representation of the tumor and its spatial relationship with the surrounding tissue. The segmented regions from these planes will then be interpolated (using the interpolation tool in ITK-SNAP) to construct a 3D representation of the entire tumor structure. This approach allows for a detailed visualization and measurement of the tumor and its margins from multiple perspectives.

In addition to the overall tumor segmentation, the surgeons will measure the deep margin at every segmented plane. This step will provide a detailed plane-by-plane assessment of the deep margin, which is crucial for determining the adequacy of the resection. The measurements from the 3D ultrasound will then be correlated with the histopathology results to evaluate the accuracy of the ultrasound-based measurements.

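### The t-test rule for the plane-by-plane deep margins (p < 0.05 means significant correlation) does not test whether imaging follows the margin from plane to plane

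*Protocol article*

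**What the plan says.** Section 3.2.2 sets up the data. "The segmentation process will be performed on approximately 10–15 equally distanced planes throughout the tumor volume", and "the surgeons will measure the deep margin at every segmented plane". The article gives the reason: "This step will provide a detailed plane-by-plane assessment of the deep margin, which is crucial for determining the adequacy of the resection". The readings are then to be correlated with histopathology to judge how accurate they are.

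Section 5 repeats the design ("The deep margin will be measured at equally distanced planes of imaging in every case, and the results will be correlated to the corresponding" readings from the reference standard) and fixes the analysis: "Correlation between the plane-by-plane deep margin measurements obtained by the reference standard and the index tests will be evaluated by" a t-test, and "the threshold for significance correlation will be" p < 0.05.

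Two other rules in the same section bear on how this can be read:

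- For margin and volume measurements generally, "The measurement differences between the index tests and the reference standard will be compared by a paired" t-test. This is the only t-test whose type is named.
- Pearson's coefficient is used for the degree of correlation, and "the index tests and the reference standard will be considered to be significantly correlated when" p < 0.05.

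Section 5 does not say whether planes are pooled over specimens or analysed within each specimen. It names no allowance for several planes coming from one specimen.

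**The concern.** Measuring the deep margin on every plane adds something to the single smallest deep margin only if the plane readings carry information inside a specimen. The natural question is whether the imaging margin rises and falls with the histological margin from plane to plane.

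The stated rule attaches the label of significant correlation to a t-test p-value. If that p-value answers a different question, the label can be wrong in either direction. An imaging method that cannot tell one plane from another may be reported as correlated plane by plane. Under the other reading, a method that follows the planes well may be reported as not correlated.

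**Working it through.** **Inputs from the article.** Planes per specimen K = 10–15 (Section 3.2.2). Specimens N = 27 evaluable, 30 enrolled (Section 6). Threshold p < 0.05 (Section 5), taken as two-sided. The sample size is used here only as N. It reproduces from 55% versus 16% with unpooled variance: (1.960 + 1.282)² × (0.55×0.45 + 0.16×0.84) / 0.39² = 10.51 × 0.3819 / 0.1521 = 26.4, so 27 (per group, for independent proportions), and 27/0.9 = 30.

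**Assumptions, not in the article.** ICC is the share of deep-margin variance lying between specimens. rb is the correlation of index test and histology at specimen level, and rw the correlation within specimens. Both methods have the same variances. A plane-blind test has rw = 0.

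**Reading A: t-test of Pearson's r over all planes.** The number of pairs is 27×10 = 270 to 27×15 = 405, so the critical |r| is 0.119 to 0.097. The expected pooled correlation is

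r = ICC × rb + (1 − ICC) × rw,

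which for a plane-blind test is ICC × rb. At ICC 0.2 and rb 0.8 this is 0.16, above both critical values. At ICC 0.1 and rb 0.8 it is 0.08, below both. Simulated share of trials in which a plane-blind test with independent plane noise is called significantly correlated:

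| ICC | rb | K = 10 | K = 15 |
|---|---|---|---|
| 0 | – | about 5% | about 5% |
| 0.1 | 0.8 | 26% | 35% |
| 0.2 | 0.8 | 68% | 81% |
| 0.3 | 0.5 | 63% | 72% |
| 0.3 | 0.8 | 92% | 97% |
| 0.5 | 0.5 | 88% | 93% |
| 0.5 | 0.8 | over 99% | over 99% |

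At ICC 0.2 and rb = 1 (between-specimen SD 0.5 mm, within-specimen SD 1 mm: 0.25/1.25 = 0.2) the share is 90% with 12 planes.

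Two separate faults are at work.

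1. *Dependence.* With no correlation at either level (rb = rw = 0) and ICC 0.5, the variance of r is inflated by about 1 + (K − 1) × ICC². That is 1 + 9×0.25 = 3.25 for K = 10 and 1 + 14×0.25 = 4.5 for K = 15. The usual limit of 1.96 then acts like 1.96/√3.25 = 1.09 or 1.96/√4.5 = 0.92, giving about 28% and 36% false significance. Simulation gives 30–38%.
2. *Wrong quantity.* Correcting the standard error does not cure the second fault. With 12 planes, within-specimen SD 1 mm, rb = 1 and between-specimen SD 0.5, 1 and 2 mm, a cluster-robust test of the pooled slope still rejects for a plane-blind test in 80%, 100% and 100% of trials.

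**Reading B: paired t-test.** The null is a mean difference of zero, and correlation does not enter it. With 12 planes:

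- An unbiased index test that follows the planes (independent noise SD 0.5 mm) has p < 0.05 in 4–5% of trials. With correlation 0.95 at both levels, so that it also carries specimen-level error, the share is 44%. It would usually be called not correlated.
- A plane-blind test with a 1 mm bias has p < 0.05 in 100%, and would be called correlated.
- An unbiased plane-blind test with rb = 1 has p < 0.05 in about 4–7%.

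**Within-specimen analysis.** Take the correlation inside each specimen, transform by Fisher's z, and test the 27 values against zero. With 12 planes this rejects in 5.3% when rw = 0, in 89% when rw = 0.2 and in 99.9% when rw = 0.3.

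**The case against.** The strongest reply is that the article does not say the planes are pooled. Planes are measured in every case and matched to the corresponding histology, so a Pearson test run separately in each specimen is a third reading, and it would have the right null. This stands as a possibility. But the article gives one threshold, no per-specimen step, and no way to combine some 27 results.

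Second, the article states no null of zero within-specimen association and attaches no success criterion to this analysis. The plane-by-plane deep margin is not named among the outcomes in Section 4, where the image-by-image item is depth of invasion. The stated aim is accuracy, for which differences between patients are legitimate signal, and Bland–Altman plots are also planned. This also stands. A reader might infer that the trial declares success on this p-value; the article supports only that it declares a significant correlation. Nor are the Reading A rates type I errors of the pooled test when rb is above zero, because the pooled correlation is then truly non-zero. They show that the pooled test answers another question.

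Third, a reader might infer that a plane-blind test will almost always pass. The article does not support that. The rate depends on ICC and rb, which it does not give; it is about 5% with no between-specimen variance, and an unbiased plane-blind test with rb = 1 does not usually pass a paired t-test.

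Finally, a condensed article may leave model details to a fuller document. Here, though, it names a test and a decision rule, and that rule can be judged as written.

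**Conclusion.** The point holds in a limited form. As written, the t-test rule does not test plane-level correspondence. Read as a paired t-test, significance marks mean bias, and the label of correlation can be the reverse of the truth. Read as a pooled Pearson test, it ignores the clustering of 10–15 planes per specimen and can be significant from specimen differences alone. For a plane-blind test the pooled rate runs from about 5% (no between-specimen variance) through roughly 70–90% (ICC 0.2, rb 0.8–1) to about 90% or more (ICC 0.5, rb at least 0.5).

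These sizes rest on 27 specimens, normal data, equal variances for both methods and assumed values of ICC and rb. That pooling is intended is an inference. The mismatch between the rule and the question does not depend on the assumed variances under either of these two readings.

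**What to change.** Delete the t-test rule for this analysis in Section 5 and replace it with wording such as: *Plane-level correspondence of the deep margin will be assessed within specimens by a mixed model of the index margin on the reference margin, with the reference split into the specimen mean and each plane's deviation from it. The within-specimen slope, or a repeated-measures correlation, will be reported with a 95% confidence interval that takes the specimen as the cluster. The between-specimen association will be reported separately.*

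If a separate Pearson analysis in each specimen was intended, the section should say so and state how the specimen results are combined.

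The cost is one or two sentences. The data are the same, standard R functions suffice, and the planned number of specimens is adequate for a modest within-specimen correlation under the assumptions above. The small downside is that the within-specimen figure may be lower than the pooled r and so look less favourable.
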